### Follow-Up Rate

Based on our previous experience in similar studies conducted at our center [19, 20], we anticipate a loss to follow-up rate of 10–20% after 3 years. Measures will be taken to minimize attrition, including scheduled follow-up reminders and coordination with clinical teams to ensure patient engagement throughout the study period.

### Statistical Analysis

#### Sample Size

Based on the previous literature of study cohorts which are similar to our expected study population [21–23], our hypothesis is that at 3 years the tailored group will have a 5% higher %TWL in comparison to the fixed group (40% vs. 35%). In order to detect a difference in %TWL at 3 years with a power of 0.8 and an alpha significance of < 0.05 and standard deviations of 12, 90 patients are needed in each arm for a total of 180 patients. Assuming a drop-out rate of 10%, enrollment of 198 patients is needed for sufficient power for the trial.

### Data Analysis

Statistical analysis will be performed using IBM SPSS Statistics software version 29. Continuous variables will be presented as means ± standard deviations, and categorical variables will be presented as frequencies and percentages. Baseline characteristics of the two groups will be compared using independent *t*-tests for continuous variables and chi-square tests for categorical variables.

The primary outcome (%TWL) will be compared between the two groups using an independent *t*-test. If data are not normally distributed, a Mann–Whitney *U* test will be used. Changes in obesity-related diseases and quality of life scores will be analyzed using paired *t*-tests or Wilcoxon signed-rank tests (as appropriate) to compare pre- and post-operative values within each group. Differences between groups will be assessed using independent *t*-tests or Mann–Whitney *U* tests. The incidence of complications will be compared between the two groups using chi-square tests or Fisher’s exact tests.

Multivariable regression analysis will be used to adjust for potential confounders (e.g., baseline BMI, comorbidities) in the analysis of the primary outcome. A *p*-value of < 0.05 will be considered statistically significant.

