### Data Collection

Data will be collected prospectively at baseline, intra-operatively, and during follow-up visits.

The following data points will be collected:Demographics: Age, genderPre-operative: Weight, height, Body Mass Index (BMI), obesity-related conditions, previous abdominal surgeries, ASA score, Charlson comorbidity index (CCI), blood test results (hemoglobin, platelets, creatinine, albumin, vitamin D, B12, folic acid, iron, ferritin, transferrin, glucose, HbA1c, lipid profile, liver, thyroid and parathyroid function tests)Intra-operative: Date of surgery, duration of surgery, total small bowel length (cm), BPL length (cm), intra-operative complications.Post-operative: Post-operative complications (bleeding, leak, wound infection, VTE, surgical site infection), grading of complications according to Clavien-Dindo grading of complications [13], length of hospital stay, 90-day readmissions, 90-day reoperations.Follow-up (6 months, 1 year, 3 years): Weight, height, BMI, obesity-related conditions during follow-up, blood test results (as above), > 90-day complications, reoperations, quality of life measures will be measured according to the BAROS questionnaire [14]. Bowel habits and stool characteristics will be assessed according to the Fecal Score [15].

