### Secondary Outcomes

Difference in length of BPL and TSBL between the two groups.Changes in obesity-related diseases (diabetes, hypertension, dyslipidemia, sleep apnea) at 6 months and 1 year after OAGB. Remission of obesity-related diseases will be defined according to standard clinical criteria. In general, remission is considered when the patient is asymptomatic, no longer requires disease-specific medication, and relevant laboratory values are within normal limits. For example, type 2 diabetes remission will be defined as HbA1c < 6.5% without the use of antidiabetic medication, as per ADA criteria. Similar criteria will be applied for hypertension, dyslipidemia, and other obesity-related diseases, based on established clinical guidelines [16–18].Postoperative complications after OAGB—bile reflux, marginal ulcers, internal hernia, anastomotic strictures, and others—will be screened and compared.Incidence of nutritional complications (protein malnutrition, vitamin deficiencies) during the follow-up period.Changes in quality of life, as measured by the BAROS questionnaire at 6 months and 1 year post-surgery.

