### Quality of Life Measures

#### MA-II Questionnaire

We will use the Moorehead-Ardelt Quality of Life Questionnaire II (MA-II), which is part of the Bariatric Analysis and Reporting Outcome System (BAROS), to assess quality of life at 6, 12 and 36 months postoperatively. The BAROS system was originally introduced in the 1990 s and was updated in 2009. The revised MA-II includes six questions evaluating self-esteem, physical activity, social life, work conditions, sexual activity, and the individual’s relationship with food. All six questions are equally weighted, with each item assigned a score of 0.5 points. A 10-point Likert-type scale is now utilized in the scoring system. As in the original BAROS questionnaire, the updated version maintains a weighted structure, with a central neutral value of 0 and positive or negative changes represented to the right and left, respectively.

Based on the final score, outcomes are categorized into five groups: failure (≤ 0), fair (0.1–1.5), good (1.6–3.0), very good (3.1–4.5), and excellent (4.6–6.0 points).

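### The change-in-quality-of-life outcome and its paired pre/post tests have no preoperative score to work from, although arms can still be compared on postoperative scores

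*Protocol article*

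**What the plan says.** All of the relevant text is in the protocol article.

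- **Secondary Outcomes** names the endpoint as a change: "Changes in quality of life, as measured by the BAROS questionnaire at 6 months and 1 year post-surgery".
- **Data Analysis** says "Changes in obesity-related diseases and quality of life scores will be analyzed using paired" t-tests or Wilcoxon signed-rank tests, the purpose being "to compare pre- and post-operative values within each group". It then adds a comparison of the arms: "Differences between groups will be assessed using independent" t-tests or Mann–Whitney tests.
- **Data Collection** itemises the preoperative data: body measurements, obesity-related conditions, surgical history, ASA and Charlson scores, and a long list of blood tests. No quality-of-life instrument is among them. The questionnaire appears only in the follow-up entry (6 months, 1 year, 3 years): "quality of life measures will be measured according to the BAROS questionnaire".
- **MA-II Questionnaire** gives the schedule, "to assess quality of life at 6, 12 and 36 months postoperatively", and the scoring, "All six questions are equally weighted, with each item assigned a score of 0.5 points", on a scale centred on zero. It then sorts the final score into five bands, of which the top two are "very good (3.1–4.5), and excellent (4.6–6.0 points".

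**The concern.** A change score and a paired test both need a value from before surgery. The article fixes the analysis, the data list and the assessment times, and they do not fit together. This is therefore a conflict within the text, not a detail left to a fuller document.

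The Abstract includes in its aims that the tailored limb should not harm quality of life. Without a preoperative score, the trial cannot show whether patients in either arm ended up better or worse than they started. The gap also cannot be closed afterwards, because a preoperative score cannot be collected once the patient has had surgery.

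Two further mismatches concern the same outcome: the bands do not fit the item scoring printed just above them, and the sections disagree on how long quality of life is followed.

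**Working it through.** **1. What the paired analysis needs and what is collected.** For each patient the quantity analysed is D(t) = Y(t) − Y(pre), where Y is the questionnaire score.

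| Quantity | Source | Assessments listed |
|---|---|---|
| Y(pre) | Data Collection, preoperative entry; MA-II Questionnaire | 0 |
| Y(t) | Data Collection, follow-up entry; MA-II Questionnaire | 3 (6, 12 and 36 months) |

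With no Y(pre), the number of complete pre/post pairs at each follow-up time is 0. The change outcome and the within-group paired test therefore have no data.

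**2. What the between-arm analysis needs.** A comparison of Y(t) between arms at a given time needs postoperative scores only, and these are scheduled at all three times. Because allocation is randomised, this is a valid treatment comparison without a baseline. The sentence in Data Analysis on differences between groups does not say whether it means postoperative scores or change scores. Only the first can be computed.

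**3. The other variable in the same paired analysis.** Data Analysis applies the paired tests to obesity-related diseases as well. Those conditions are in the preoperative list and in the follow-up list, so that part does not lack its baseline.

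**4. The score bands.** Inputs from MA-II Questionnaire: 6 items, 0.5 points each, neutral value 0.

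- Maximum = 6 × 0.5 = 3.0. Reading 0.5 as the limit on each side of zero, the minimum is −3.0.
- Failure (≤ 0), fair (0.1–1.5) and good (1.6–3.0) can be reached.
- Very good starts at 3.1 and excellent at 4.6. Both exceed 3.0, so 2 of the 5 bands cannot be reached by this score, and a perfect score falls in the good band.
- The stated top of 6.0 is not reproduced. It would need 6.0 / 6 = 1.0 point per item, or further components in the total. The article states neither.

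**5. Time points.** Secondary Outcomes lists 6 months and 1 year. Data Collection and MA-II Questionnaire list both of these and 36 months. The 36-month score is collected but does not belong to the named outcome.

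**The case against.** The strongest reply is that quality of life remains analysable. The arms can be compared on postoperative scores, which is the comparison that randomisation supports, whereas a within-group paired test does not compare the treatments. That stands. A reader might infer that the whole quality-of-life endpoint is lost, or that none of the planned paired tests can be run. The documents support neither, as the second and third steps of the check show.

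It can also be said that the article merely left an item off its list: Data Collection speaks of data at baseline, and the paired test presupposes a preoperative score. That is possible. But the list is detailed and the questionnaire schedule is given in two places, both postoperative only, so the text still needs correcting.

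On the bands, a reader might infer that high scorers will be misclassified in the results. No planned test or listed outcome uses the bands. The MA-II is described as part of BAROS, so the bands may belong to a larger BAROS total. The article does not define such a total, and it places the bands under the MA-II heading. What remains is a need to say which score they classify.

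The Fecal Score also has no baseline, and a reader might count that as the same contradiction. It is not: no pre/post test is planned for it, and it is not listed as a secondary outcome.

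Finally, it is tempting to add a loss of precision from not adjusting for baseline. With a correlation of 0.3 to 0.5 between baseline and follow-up scores, the variance reduction forgone would be 0.3² = 9% to 0.5² = 25%. Those correlations are assumptions with no source in the article, and Data Analysis plans covariate adjustment for the primary outcome only. The point does not rest on this.

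**Conclusion.** The point holds for the change-in-quality-of-life outcome and the within-group paired quality-of-life tests. As written, there are no preoperative scores against three postoperative assessments, so neither can be produced. It does not extend to the between-arm comparison of postoperative scores, the paired analysis of obesity-related diseases, or the primary weight-loss outcome.

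The band mismatch (a maximum of 3.0 against a top band ending at 6.0) and the differing time points are real but secondary. The first is a question of which score is being classified, and the second is a matter of wording.

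The conclusion assumes that the preoperative list and the two schedules describe what will be done. If a preoperative questionnaire is in fact collected, only the text needs correcting. Either way this should be fixed, but it is not critical, because only a secondary outcome is affected.

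**What to change.** 1. Add the MA-II to the preoperative entry in Data Collection and to the schedule in MA-II Questionnaire. Because patients are not blinded, have it completed before the allocation is known to them.
2. In Data Analysis, compare the arms on the continuous MA-II score adjusted for its baseline value.
3. For any patients already operated on without a baseline, compare postoperative scores between arms only and drop the paired test. The article does not say whether there are such patients.
4. State whether the five bands classify the MA-II alone or a BAROS total. If a total, define its components. Do not apply the bands to the MA-II alone as printed. New cut-offs for a score ending at 3.0 would need supporting evidence that the article does not contain.
5. Align the time points in Secondary Outcomes with Data Collection and MA-II Questionnaire by including 36 months, or say why the outcome stops at 1 year.

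A baseline Fecal Score could be taken at the same visit, but this is optional.

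The cost is one six-item form at a preoperative appointment that already takes place, plus changes of wording. No procedure is added and the sample size does not change.

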The outcomes of patients after OAGB with a tailored BPL length are unclear. It is possible that these patients could have higher weight loss and metabolic outcomes. The purpose of this study is to evaluate if personalized tailoring of the BPL length to TSBL is effective and safe. Our primary outcome will investigate if tailored BPL is more effective in terms of percentage of total weight loss at 3 years compared to patients undergoing OAGB with a standard BPL length. We will also record perioperative and malnutrition-related outcomes in order to investigate the safety profile of the tailored BPL arm in comparison to the standard arm. We hypothesize that tailoring the BPL length to a percentage of the TSBL in patients undergoing OAGB will result in greater total weight loss after 1 and 3 years and result in comparable safety outcomes, including perioperative and malnutrition-related complications, compared to a fixed standard BPL length. We hereby present the protocol of the *T*ailored *B*iliopancreatic *L*imb *LE*ngth to 40% of TSBL study (TABLE-40 study).

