### Follow-Up

Participants will be followed up at 2 weeks, 3 months, 6 months, 12 months, and annually thereafter. At each visit, weight, obesity-related diseases, and any complications will be assessed. Blood tests will be performed at 3–6 month intervals to monitor nutritional status.

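### Crude chi-square/Fisher comparison is fixed for complications that accrue over 3 years despite 10–20% expected loss, so the result depends on how lost patients are counted

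*Protocol article*

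**What the plan says.** The Data Analysis section names one method for all complications: "The incidence of complications will be compared between the two groups using chi-square tests or Fisher’s exact tests". It makes no exception for late outcomes and names no method that uses follow-up time.

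The outcomes covered are partly long-term. Secondary Outcomes lists "Incidence of nutritional complications (protein malnutrition, vitamin deficiencies) during the follow-up period", and also "bile reflux, marginal ulcers, internal hernia, anastomotic strictures, and others", neither with a fixed time point. Data Collection records complications beyond 90 days at 6 months, 1 year and 3 years. On visits, the Follow-Up section says: "Participants will be followed up at 2 weeks, 3 months, 6 months, 12 months, and annually thereafter".

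The Follow-Up Rate section says of attrition: "we anticipate a loss to follow-up rate of 10–20% after 3 years". The Introduction hypothesises that the tailored limb will "result in comparable safety outcomes, including perioperative and malnutrition-related complications, compared to a fixed standard BPL length".

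**The concern.** A chi-square or Fisher test needs a yes/no status for each patient over one common period. That suits perioperative and 90-day outcomes. It does not suit outcomes that build up over 3 years when the plan itself expects up to a fifth of patients to leave early. A patient lost at 13 months without an event has been observed for about a third of the period. A crude proportion must count that patient as a full 3-year non-event or leave the patient out.

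The late outcomes bear directly on the safety question. Patients with a total small bowel length below 450 cm are excluded, and 40% of 450 cm is 180 cm. Every eligible tailored limb is therefore at least as long as the control limb. The Introduction also cites a review in which limb length affected nutritional deficiency more than weight loss. Any safety cost of tailoring would thus most plausibly appear in the nutritional and late outcomes. Patients are not blinded, so loss could differ between arms.

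**Working it through.** **Inputs from the protocol.** Loss by 3 years is 10–20% (Follow-Up Rate). Enrolment is 198, or 99 per arm (Sample Size, with balanced allocation).

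**The plan's own figure.** The protocol gives no figure for complications. Its only calculation is for percentage total weight loss: n per arm = 2 × (1.96 + 0.842)² × 12² / 5² = 90.4, so 91. The stated 90 gives power 0.798 and reproduces within rounding. 180 × 1.10 = 198.

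**Assumptions.** The protocol gives no event risks. I take true 3-year risks of 10% (standard) and 20% (tailored) for illustration, and constant event and loss hazards that are independent unless stated otherwise.

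**Formulas.** Let p be the true 3-year risk and d the proportion lost by 3 years.

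- *Lost counted as event-free, loss spread over 3 years:* observed risk = a/(a + c) × [1 − (1 − p)(1 − d)], with a = −ln(1 − p) and c = −ln(1 − d).
- *Lost counted as event-free, all loss just after year 1:* observed risk = (1 − d)p + d × F(1), with F(1) = 1 − (1 − p)^(1/3).
- *Completers only:* p if loss is independent. If lost patients have k times the risk of those retained, p / [(1 − d) + dk].
- *Completers plus patients with an event before loss:* obs / [obs + (1 − p)(1 − d)], where obs is the first formula.

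Example for 20% loss just after year 1:

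- p = 0.20: 0.8 × 0.20 + 0.2 × 0.0717 = 0.1743.
- p = 0.10: 0.8 × 0.10 + 0.2 × 0.0345 = 0.0869.
- Difference: 8.74 points.

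| How lost patients are counted | Loss in both arms | Standard (true 10%) | Tailored (true 20%) | Difference (true 10.0) |
|---|---|---|---|---|
| Event-free, loss spread over 3 years | 10% | 9.50% | 19.02% | 9.52 |
| Event-free, loss spread over 3 years | 20% | 8.98% | 18.00% | 9.02 |
| Event-free, loss just after year 1 | 20% | 8.69% | 17.43% | 8.74 |
| Completers only, independent loss | 10% or 20% | 10.00% | 20.00% | 10.00 |
| Completers only, lost at twice the risk | 20% | 8.33% | 16.67% | 8.33 |
| Completers only, lost at half the risk | 20% | 11.11% | 22.22% | 11.11 |
| Completers plus earlier events | 10% | 10.50% | 20.90% | 10.40 |
| Completers plus earlier events | 20% | 11.09% | 21.95% | 10.86 |

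**Size against sampling error.** The standard error of the difference with 99 per arm is √[(0.10 × 0.90 + 0.20 × 0.80)/99] = 5.03 points. The shrinkage of 10.00 − 8.74 = 1.26 points is 0.25 standard errors. With 20% loss spread over 3 years it is 0.98 points, about 0.20. Power for 10% vs 20% is 50.4% with no loss and 45.9% with 20% loss spread over time and counted as event-free. The risk ratio stays near 2.0 under equal independent loss.

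**Unequal loss (counted as event-free, spread over 3 years).**

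- Standard arm loses 10%, tailored 20%: 18.00 − 9.50 = 8.50 points.
- Reversed: 19.02 − 8.98 = 10.04 points.
- Equal true risks of 10%: the arm losing 20% reads 8.98% and the arm losing 10% reads 9.50%. Whichever arm loses more looks 0.52 points safer.

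**The case against.** Four objections have force.

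*Direction.* A reader might infer that crude risks will be too low and that the arm difference will shrink toward comparable safety. The protocol does not support that as a certainty. It follows if lost patients stay in the denominator as event-free, or if completers only are analysed and those lost had higher risk. No section says either. Other counts give no bias or upward bias. Nor does unequal loss necessarily flatter the tailored arm, because nothing in the protocol says which arm would lose more.

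*Silence.* A reader might also treat the absence of a scoring rule for lost patients as the defect. A condensed article may leave denominators to the full protocol or analysis plan, so that absence is no finding. What remains is the stated choice of a test that takes no account of follow-up time.

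*Size.* These are secondary outcomes and the bias is modest. Low power is a larger reason why a non-significant test could be misread as comparable safety: with 99 per arm it is about 50% for 10% vs 20%, and about 27% for 5% vs 10%.

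*Alternatives.* Comparing proportions at common visits (6 months, 1 year, 3 years) by chi-square is legitimate, and vitamin deficiency is a laboratory state that may exist before surgery. But the nutritional outcome is named as incidence over the follow-up period, not as status at a visit. Prevalence at a visit is a different quantity, and it still omits those already lost. Censoring also assumes independent loss, so a sensitivity analysis is needed with either method.

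**Conclusion.** The concern holds in a limited form. The article fixes a crude-proportion test for all complications, including those that accrue over 3 years, while expecting 10–20% loss by then. The same sentence permits several counts that bias late risks in different directions.

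If lost patients count as event-free, risks and the risk difference fall by about 5–10% in relative terms when equal loss is spread over 3 years, and by about 13% when a 20% loss falls just after year 1. Completers-only analysis is unbiased only under independent loss, and it discards events seen before loss. Completers plus earlier events overstates risks. Unequal loss can move the difference either way.

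These sizes rest on assumed event risks and constant hazards; only the loss range is the protocol's. Perioperative and 90-day comparisons are hardly affected. The change is worth making because the affected outcomes carry the long-term safety claim and a better method costs little.

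**What to change.** Keep chi-square or Fisher's exact tests for perioperative and 90-day complications.

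For nutritional complications and complications after 90 days:

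- Estimate 3-year cumulative incidence per arm from surgery to first new event.
- Censor at last assessment, and treat death or reversal of the bypass as competing events.
- Report the risk difference with a 95% confidence interval.
- Add a sensitivity analysis for informative loss, for example with lost patients at higher or lower risk than those retained.

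The cost is analysis wording only, since scheduled visits and blood tests at 3–6 month intervals already supply approximate dates. There are three small downsides. Event dates are known only to the nearest visit. Censoring still assumes that loss is independent of the event. Deficiencies present at baseline must be excluded or handled separately; pre-operative blood results are collected, so they can be identified.

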Consent will be documented using a digital form via an institutional application, with a paper form available as a backup. Following consent, participants will be randomly assigned to either the tailored BPL group (40% of TSBL) or the standard BPL group (180 cm) using a computer-generated sequence to ensure balanced allocation. Block randomization will be employed to ensure balanced allocation between the study arms throughout the recruitment period. Variable block sizes will be used to minimize predictability and maintain allocation concealment. Patients are not blinded to treatment allocation as blinding was deemed impractical and potentially misleading in this context. Stratification will not be used in the randomization process, as our study population is expected to be relatively homogeneous with regard to key baseline characteristics, and randomization is anticipated to balance these across groups. While blinding of the surgical team is not feasible due to the nature of the intervention, data collection and analysis will be performed by researchers blinded to group assignment whenever possible.

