### Outcome Measures

#### Primary Outcome

The primary outcome is the difference in percentage of total weight loss (%TWL) between the two groups at 1 and 3 years postoperatively.

%TWL will be calculated as: (Pre-operative weight – Follow-up weight)/Pre-operative weight) × 100.

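### The primary comparison of %TWL can switch from a t-test to a rank test after a look at the data, and the adjusted regression beside it has no stated rank; one adjusted analysis of the 3-year mean difference should be named primary

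*Protocol article*

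**What the plan says.** All three analyses stand in the Protocol article, Data Analysis section:

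- The main comparison: "The primary outcome (%TWL) will be compared between the two groups using an independent" t-test. It is unadjusted.
- The replacement rule: "If data are not normally distributed, a Mann–Whitney" U test takes over. What counts as non-normal, and who decides, is not given.
- The adjusted analysis: "Multivariable regression analysis will be used to adjust for potential confounders (e.g., baseline BMI, comorbidities) in the analysis of the primary outcome". The covariates are illustrations, and the section does not say whether this result stands above, beside or below the t-test.

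A single threshold of p < 0.05 covers everything.

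Three other sections bear on the choice:

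- Sample Size rests on a difference in mean %TWL at 3 years: 40% against 35%, SD 12, power 0.8, 90 evaluable per arm, 198 enrolled.
- Follow-Up sets the visits: "Participants will be followed up at 2 weeks, 3 months, 6 months, 12 months, and annually thereafter". Weight is assessed at each of them.
- Follow-Up Rate states: "we anticipate a loss to follow-up rate of 10–20% after 3 years".

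**The concern.** The choice between t-test and Mann–Whitney is made after the outcome data are seen, on a check that is not defined. It also changes the question. The trial is sized to detect a 5-point difference in means, and the Mann–Whitney test neither estimates nor tests that difference. If it were triggered, the reported primary p-value would no longer belong to the quantity in the sample-size section. Because the primary outcome is placed at both 1 and 3 years, the two years could even be reported by different tests.

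The regression adds a second result for the same outcome, with a covariate list that can still be chosen. If the unadjusted and adjusted results fall on opposite sides of 0.05, the text does not settle which one is the trial's answer.

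Precision is a separate matter. The t-test at 3 years uses neither baseline BMI nor the earlier weights, in a trial planned at 80% power with no margin and an expected loss of up to one participant in five.

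**Working it through.** **Inputs from the Protocol article.** Difference 5 points, SD 12, alpha 0.05 (taken as two-sided), power 0.8, 90 evaluable per arm, 198 enrolled (99 per arm), loss 10–20% at 3 years.

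**Assumed inputs, not in the document.** Correlation of baseline covariates with 3-year %TWL: 0.1 to 0.4. Correlation of 1-year with 3-year %TWL: 0.3 to 0.8.

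**Step 1: the plan's own figure.** n per arm = 2 × 12² × (1.960 + 0.842)² / 5² = 90.4, so 91. With the t distribution it is 91.4, so 92. The stated 90 is close enough; its power is 0.798 by the normal approximation and 0.794 by the noncentral t. The powers below use the noncentral t.

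**Step 2: t-test on the participants weighed at 3 years.**
- 10% loss: 99 × 0.9 = 89.1 per arm, power 79%.
- 20% loss: 99 × 0.8 = 79.2 per arm, power 74%.

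**Step 3: baseline adjustment.** A covariate with correlation r reduces the SD to 12 × √(1 − r²), which is equivalent to n / (1 − r²) per arm. At 20% loss (79 per arm):

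| r | equivalent n per arm | power |
|---|---|---|
| 0 | 79 | 74% |
| 0.1 | 79 / 0.99 = 79.8 | 74% |
| 0.3 | 79 / 0.91 = 86.8 | 78% |
| 0.4 | 79 / 0.84 = 94.0 | 81% |

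**Step 4: use of the 1-year weights.** Suppose a fraction m is lost between 1 and 3 years and the correlation is r. A likelihood-based repeated-measures analysis then has variance factor (1 − r²)/(1 − m) + r², and effective n = 99 / factor.

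| m | r | factor | effective n per arm | power |
|---|---|---|---|---|
| 0.2 | 0.3 | 1.2275 | 80.7 | 75% |
| 0.2 | 0.5 | 1.1875 | 83.4 | 76% |
| 0.2 | 0.7 | 1.1275 | 87.8 | 78% |
| 0.2 | 0.8 | 1.0900 | 90.8 | 80% |
| 0.1 | 0.3 | 1.1011 | 89.9 | 79% |
| 0.1 | 0.5 | 1.0833 | 91.4 | 80% |
| 0.1 | 0.7 | 1.0567 | 93.7 | 81% |
| 0.1 | 0.8 | 1.0400 | 95.2 | 82% |

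**Step 5: size of the selection problem.** In simulated trials with no effect (90 per arm, 5,000 per scenario, share of variance explained by baseline 0.05–0.30, 1-year/3-year correlation 0.5–0.7), the 3-year t-test alone is significant in about 5%. If the best of t-test, Mann–Whitney and adjusted regression at 3 years could be picked freely, the figure is about 6.5–8%, so method choice adds about 1.5–3 points. This is an upper bound: the plan does not allow free choice among all three.

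**The case against.** The strongest reply is that the plan does have a main test. On a plain reading the t-test is primary, the Mann–Whitney test replaces it rather than running beside it, and the regression is supportive. That is fair. A reader might infer three competing primary p-values; the text supports at most two per time point, and the type I error from choosing among methods is small. What stands is that the replacement rule depends on undefined features of the outcome data and that the regression's rank and covariates are left open in a sentence that places it within the primary-outcome analysis.

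Four stronger readings are tempting, and the document does not support them:

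- *The analysis is restricted to completers.* No analysis set or missing-data method is stated, and an article may leave both to the full protocol or SAP. A 3-year t-test with enrolment inflated for dropout suggests it but does not say it.
- *Baseline data are wasted.* %TWL is already scaled by pre-operative weight, and the regression names baseline BMI. The fault is only that the adjusted model is not made primary.
- *Analysing those with a 3-year weight must be biased.* If loss follows 1-year weight loss by the same rule in both arms, a simulation with about 20% loss and correlation 0.7 left the arm difference at 0.0 under no effect, and at about 4.6 for a true 5. Material bias generally needs dropout that differs by arm, which nothing in the document indicates.
- *Randomisation must be stratified by centre.* The article gives its reason: "Stratification will not be used in the randomization process, as our study population is expected to be relatively homogeneous". That is a deliberate design choice and a separate question. Nor can one say centre is barred from the regression, since its covariates are only examples.

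It is also fair that the t-test is valid in a randomised trial, and that a single prespecified baseline-adjusted linear model would cure the ranking problem as well as a repeated-measures model would.

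**Conclusion.** The point holds in a limited form. The stated text fixes the primary analysis badly: a data-triggered switch leaves the mean difference that the trial is sized on, for little benefit at about 80–90 per arm, and an adjusted regression with an open covariate list sits beside it unranked.

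The precision argument supports the change but is modest, and it rests on correlations the document does not give. At 20% loss, power of about 74% becomes 74–81% with baseline adjustment (correlations 0.1–0.4) or 75–80% with 1-year weights (correlations 0.3–0.8). At 10% loss, about 79% becomes 79–82% with 1-year weights. At the low end of these ranges the gain is negligible. A repeated-measures model has one further advantage: it allows loss to depend on earlier observed weight.

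**What to change.** Name one primary analysis at 3 years, the time point used for sizing. It can be a linear model of 3-year %TWL, or a repeated-measures model of %TWL over the scheduled visits with the 3-year contrast as the result. Fix the covariates in advance (baseline BMI and centre), describe them as prognostic covariates rather than confounders, and report the mean difference with its 95% CI. Remove the normality-triggered switch, and keep the unadjusted t-test and the Mann–Whitney test as sensitivity analyses.

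The cost is wording in the analysis section, agreed before outcome data are compared by arm, and slightly more modelling work. No extra data are needed, since the weights are already scheduled, and SPSS, the named software, has the procedures.
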